# Pre-operative anxiolysis in children through a combined pharmacological therapy with hydroxyzine and a non-pharmacological distraction technique with a clown (SONRISA): study protocol for randomised double-blind clinical trial

**DOI:** 10.1186/s13063-019-3906-2

**Published:** 2020-01-02

**Keywords:** Anxiety, Surgery, Clown, Hydroxyzine, Randomised clinical trial

## Abstract

**Background:**

Surgery can generate significant stress and anxiety in up to 70% of the paediatric population. There are several pharmacological and non-pharmacological strategies to reduce pre-operative anxiety in children, however, they have several side effects and the available information about them is contradictory. The role of clowns and hydroxyzine in the management of anxiety is controversial, with some studies supporting and others contraindicating both strategies.

**Methods:**

We propose a randomised double-blind, controlled clinical trial that will evaluate the effectiveness of both interventions (hydroxyzine and clowns), alone or in combination, to reduce pre-operative anxiety (using the modified Yale scale of preoperative anxiety) in children aged 2–16 years undergoing outpatient surgery (*n* = 188).

Subjects will be randomised into two groups – (1) standard procedure (parental accompaniment) combined with placebo or (2) standard procedure combined with preoperative hydroxyzine. After randomisation, they will be divided by chance into two further groups, depending on the presence of clowns on the patient’s surgery day. Control of pre-operative anxiety will be determined in the four groups by a modified Yale scale of preoperative anxiety and cortisol levels. Compliance of children during induction of anaesthesia, time until anaesthesia recovery, presence of postoperative delirium and use of analgesia until discharge will be also assessed. For additional information, the children, parents and healthcare professionals involved in the study will complete a satisfaction survey.

**Conclusions:**

This study aims to gather evidence on which of these four therapeutic options achieves the highest reduction of pre-operative anxiety with the best safety profile to allow paediatricians and anaesthesiologists to use the most effective and safe option for their patients.

**Trial registration:**

ClinicalTrials.gov identifier: NCT03324828. Registered 21 September 2017.

## Background

Surgery can generate significant stress and anxiety in up to 70% of the paediatric population [1]. The need to have specific programmes to reduce the anxiety of children is of special interest if we consider the adverse effects of surgery associated with high preoperative anxiety (POA) [2]. High levels of POA are responsible for increased surgical morbidity [3], postoperative analgesia needs [4], and increased number of days of hospitalisation and rate of complications [1]. The management of POA in paediatric patients is a field under constant review, with the studies published to date having differing, controversial and non-conclusive results [5, 6].

**Fig. 1 Fig1:**
[figure not shown]
Example template of recommended content for the schedule of enrolment, interventions and assessments. M0 (Moment 0): baseline status upon arrival at the presurgical hospitalisation area; M1 (Moment 1): stay in the pre-surgical hospitalisation area; M2 (Moment 2): moment when the patient is transferred to the operating room up to the entrance to the surgical ward and parental separation; M3 (Moment 3): time during the induction of anaesthesia in the operating room; PACU (Post-Anaesthetic Resuscitation Unit): upon arrival at PACU and until recovery from anaesthesia. *ICC* Induction Compliance Checklist; *m-YPAS* modified Yale Preoperative Anxiety Scale

In order to reduce POA, strategic programmes that try to minimise the emotional impact have been designed. Some of these strategies are parental accompaniment during induction of anaesthesia [5, 6], sedative premedication [7] and distraction techniques [8, 9], including the presence of clowns [10] or music therapy [11].

Pharmacological studies performed with preoperative anxiolytic medication assess off-label drugs (such as clonidine) or drugs that require close monitoring and control measures (as midazolam) due to associated serious adverse events like delirium and respiratory depression [12, 13]. Hydroxyzine is an antihistamine with sedative properties approved for anxiolytic use both in Europe and the USA. Despite its widespread use in clinical practice, only few studies have assessed hydroxyzine’s effectiveness, most of which have been in the context of minor odontology interventions [14–16]. Furthermore, there are no clinical trials about its use for the management of POA in major outpatient paediatric surgery.

Studies related to non-pharmacological techniques for POA management have been published [5, 6, 8–11, 17] but results related to effectiveness of accompaniment and distraction are not confluents either [9, 17].

Humour and laughter have characteristics that could help reduce pain and stress but the information available is controversial; they seem to reduce anxiety in the area of hospitalisation prior to the operation room, but it has not yet been possible to demonstrate their benefit as anxiolytic therapy within the surgical area [18]. In a study by Vagnoli et al., 40 children aged between 5 and 12 years undergoing paediatric ambulatory surgery were randomised either to distraction and accompaniment by clowns and parents (experimental group) or to parental accompaniment only (control group). The experimental group showed significantly less anxiety during the induction of anaesthesia than the control group. According to a healthcare professional survey, professionals consider that clowns are beneficial for the children, however, most of the professionals believe that the presence of clowns adversely affects their work and would rather not to continue with this strategy [19]. In a subsequent study, Vagnoli et al. concluded that the combination of clowns and parental accompaniment during the preoperative stage achieved a higher reduction of POA than either parental accompaniment only or oral premedication with midazolam [20].

To summarise, the role of clowns and hydroxyzine in the management of anxiety remains unknown, with studies both positive for or against it. The present study aims to address this controversy.

The main objective of this clinical trial is to show whether the combination of hydroxyzine and distracting techniques with clowns have an additive effect for the control of POA. This objective will be evaluated by a specific validated scale (modified Yale Preoperative Anxiety Scale; m-YPAS) and determination of cortisol levels. In addition, the satisfaction of patients, parents and healthcare professionals with the strategy will be evaluated by a satisfaction survey.

## Methods/design

The study was approved by the appropriate Institutional Review Board and written informed consent was obtained from all subjects, legal surrogates, parents or legal guardians for minor subjects.

The trial was registered prior to patient enrolment at ClinicalTrials.gov identifier: NCT03324828 (Principal investigator: [name], Date of registration: October 30, 2017).

### Trial design

This is a unicentric, randomised, controlled clinical trial with parallel groups double blinded for pharmacological intervention. The CONSORT guidelines for randomised controlled trials will be used. This protocol also adheres to the SPIRIT guidelines. The study schedule of enrolment, interventions and assessments are included in Fig. 1.

### Population and setting

The study will be carried out in the Hospital Clínico San Carlos (HCSC), Madrid, Spain. Patients who will undergo paediatric ambulatory surgery will be included.

### Inclusion criteria

The inclusion criteria will be the following:
Children aged between 2 and 16 years old.American Society of Anesthesiologists physical status classification grades I and II.Informed consent (IC) signed by parents or legal guardians of the minors.Specific informed consent for children aged between 12 and 16 years old.No confirmed allergies to antihistamines.

### Exclusion criteria

The exclusion criteria will be the following:
Patients who had undergone previous surgery at age 2 years or older; when children undergo operations at an age younger than 2 years old, they do not remember the surgical experience and therefore the variables analysed are not influenced by this previous experience.Patients with hypersensitivity to the active substance, to any of the excipients, to cetirizine, to other derivatives of piperazine, to aminophylline or to ethyleneamine.Patients with porphyria.Patients with diagnosed a prolongation of the QT interval.Patients with risk factors for QT interval prolongation, including pre-existing cardiovascular disease, electrolyte balance disturbances (hypokalaemia, hypomagnesaemia), family history of sudden cardiac death, significant bradycardia and concomitant use of drugs with the potential to produce prolongation of the QT interval and/or induce Torsade de Pointes.

### Randomisation

Following signature of the IC by the legal guardians of the minors and/or the child’s agreement (if applicable), randomisation to treatment with/without hydroxyzine will be performed. Randomisation will occur in a 1:1 ratio in blocks of 8. The non-blinded nurse will randomise subjects with electronic case record form (REDCap). The sequence will be blinded to all team members.

Accompaniment by clowns ([name] from Fundacion Theodora) will depend on the clown presence/availability on the day of the intervention. An alphabetical code will be assigned to patients assigned to clown accompaniment (A) or not (B).

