### Blinding

In order to hide clown accompaniment to the evaluator of the m-YPAS, their appearance on the screen will be avoided and the film will be silenced. Subjects in whose film [name] appears will be withdrawn from the study. The evaluation of all films will be done by the principal investigator.

Regarding hydroxyzine, the non-blinded nurse will administer 5 ml of juice to all subjects, mixed or not with hydroxyzine, depending on the treatment arm assigned.

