### Treatment guideline

On the day of surgery, once the IC and, if applicable, child agreements have been signed and the selection criteria have been confirmed, the non-blinded nurse will randomise the subjects. Juice, with or without hydroxyzine, will be administered to subjects at least 30 min prior to the subject being transferred to the surgical ward.

POA evaluation will be performed at the following time-points:
Time-point 0 (M0): Considered the baseline status because it is the moment when the patient arrives to the pre-surgical hospitalisation area prior to being in contact with any method to reduce POA. At this time-point, the investigators will record a film in order to evaluate the patient’s baseline state of anxiety by the m-YPAS.Time-point 1 (M1): During the stay in the pre-surgical hospitalisation area, at least 30 min after receiving the assigned strategy. At this moment, investigators will record a film to later evaluate the subject’s preoperative state of anxiety by the m-YPAS. The first Salivette® will be provided to the patient for the collection and determination of salivary cortisol. Salivette® will be collected before leaving the pre-surgical hospitalisation area.Time-point 2 (M2): Moment when the patient is transferred to the operating room up to the entrance to the surgical ward and parental separation. The investigators will record a film during the transfer to the operating room and up to the entrance to the surgical block to later evaluate a subject’s preoperative anxiety by the m-YPAS scale. At this time-point, the second Salivette® will be collected when the patient is placed in the operating room bed.Time-point 3 (M3): During the induction of anaesthesia in the operating room: The investigators will record a film during the induction of anaesthesia to later evaluate subject’s preoperative anxiety by the m-YPAS scale. At this time-point, the anaesthesiologist will complete the Induction Compliance Checklist and a blood sample (5 ml) will be obtained for cortisol analysis.Stay in Post-Anaesthetic Care Unit (PACU): Upon arrival at PACU and until recovery from anaesthesia, the variables about recovery from anaesthesia, pain, delirium, vital signs and postoperative analgesia will be collected.Stay in General Ward: at the time of hospital discharge, parents/legal guardians will complete satisfaction survey as will children aged 5 years or older. Healthcare professionals will complete this survey at the end of the study.

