### Statistical analysis

#### Sample size

Anxiety in children will be evaluated through comparing m-YPAS score between the moment of induction of anaesthesia and the presurgical moment prior to the entrance to the operating room. The sample size calculated will allow detection of a difference of means of 14.3 points at m-YPAS between the group with parental accompaniment and hydroxyzine (mean: 18; standard deviation (SD): 13.5 points) compared to the group with parental accompaniment only (mean: 32.3; SD: 24.2 points) [4, 24]. With a sample size of 47 subjects in each group, we would have a power of 90%, with a level of significance of 0.025, to detect these differences. The final sample size would be 188 subjects (47 in each group).

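### With fixed blocks of 8 and a randomising nurse who learns each allocation, about one allocation in five can be certain in advance to that role, despite the concealment statement

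*Protocol article*

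**What the plan says.** All references are to the protocol article.

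- **Trial design:** "This is a unicentric, randomised, controlled clinical trial with parallel groups double blinded for pharmacological intervention". There is one site, and no stratification factor is named.
- **Randomisation:** "Randomisation will occur in a 1:1 ratio in blocks of 8. The non-blinded nurse will randomise subjects with electronic case record form (REDCap"). One block size is given, and the person who carries out the step is not blinded. The section then states: "The sequence will be blinded to all team members". Clown accompaniment is not randomised; it follows the clowns' availability on the day.
- **Blinding:** "the non-blinded nurse will administer 5 ml of juice to all subjects, mixed or not with hydroxyzine, depending on the treatment arm assigned". The same role therefore learns each allocation.
- **Treatment guideline:** the order of steps before surgery is consent first, and then, after any "child agreements have been signed and the selection criteria have been confirmed, the non-blinded nurse will randomise the subjects".
- **Sample size:** "The final sample size would be 188 subjects (47 in each group"). The calculation compares hydroxyzine plus parents with parents only.

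**The concern.** Concealment has two parts. The unreleased list must be out of sight, and the next entry must not be deducible from earlier ones. The Randomisation section addresses the first. The design leaves the second open for one role, because the person who triggers each allocation also learns the result, and the single block size is stated.

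Hydroxyzine versus no hydroxyzine is the only randomised factor, and the sample size is built on it. If someone who can foresee the next arm could also influence which child is entered next, more anxious children could be directed towards one arm. The text describes no safeguard that separates the two abilities.

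**Working it through.** **The plan's own figure.** The plan gives no figure for predictability. The only planned number used here is the total of 188, which reproduces at a two-sided 0.025 level with 90% power:

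n per group = (2.2414 + 1.2816)² × (13.5² + 24.2²) / 14.3² = 12.411 × 767.89 / 204.49 = 46.6, rounded up to 47. Four groups give 188.

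**Inputs.** Ratio 1:1 and block size 8 (Randomisation), so each block holds 4 + 4 and there are C(8,4) = 70 equally likely orders. N = 188 (Sample size), which is 23 full blocks (184 children) plus 4 children.

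**Assumptions not stated in the article.** One role sees every allocation, knows the block size and keeps track of block boundaries. There is one unstratified list.

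**Step 1: allocations certain in advance.** Place k is certain when one arm has used all four of its places among the first k − 1. The number of such orders is 2 × C(k − 1, 4).

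| Place in block | Orders in which it is certain, of 70 | Share |
|---|---|---|
| 1 to 4 | 0 | 0% |
| 5 | 2 | 2.9% |
| 6 | 10 | 14.3% |
| 7 | 30 | 42.9% |
| 8 | 70 | 100% |

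Mean per block = (2 + 10 + 30 + 70) / 70 = 1.6 of 8, or 20%.

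**Step 2: best guess.** Always guess the arm with more places left. If a and b places remain, the guess is right with probability max(a, b) / (a + b). Averaged over the 70 orders, the values for places 1 to 8, in seventieths, are 35, 40, 40, 44, 44, 50, 50 and 70. The sum is 373 / 70 = 5.33 correct of 8, or 66.6%, against 50% by chance.

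**Step 3: scale to 188.** The last four children fall in places 1 to 4, where nothing is certain.

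- Certain: 23 × 1.6 = 36.8, about 37 of 188 (19.6%).
- Best guess: 23 × 5.329 + (35 + 40 + 40 + 44) / 70 = 122.56 + 2.27 = 124.8, and 124.8 / 188 = 66.4%.

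**Step 4: what varying the block size would change.** These figures come from 300 simulated lists of 188 per scheme. Sizes are drawn with equal probability, and the observer knows the set of sizes but not the current one.

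| Block sizes | Certain | Best guess right |
|---|---|---|
| 8 only | 19.8% | 66.7% |
| 4/6/8 | 2.4% | 68.0% |
| 6/8/10 | 1.4% | 66.5% |
| 8/12/16 | 1.7% | 64.1% |

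Varying the size nearly removes certainty but barely changes guessing. Smaller blocks make guessing slightly easier.

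**The case against.** A reader might infer that the concealment sentence is simply false, since a non-blinded nurse appears in the sentence before it. The documents do not support that. The list can stay hidden in REDCap while the nurse learns each allocation only as it is issued. Inferring some later places is not the same as seeing the list.

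A reader might also infer that the hydroxyzine contrast is biased. That is not supported either. Prediction biases entry only if the person who predicts also influences who is entered or when. The Treatment guideline puts consent and confirmed eligibility before randomisation, and nothing says that the nurse recruits, takes consent or judges eligibility. Colleagues who remain blinded cannot make the prediction. How many nurses fill the role, and who has which REDCap rights, are details an article commonly leaves to the full protocol. Their absence is no finding.

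There is further protection. M0 anxiety is filmed before any study strategy begins. The Data analysis section compares baseline characteristics and adjusts the model for clinically relevant differences. This does not replace concealment, but it could reveal gross steering on anxiety and partly correct for it.

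Finally, the percentages describe predictability, not bias in m-YPAS points, and four allocations in five are not certain in advance.

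All of this stands and limits the point. What remains is that the article itself fixes the block size, the person who randomises and the concealment claim, and together these do not secure unpredictability for that person. If several eligible children are waiting, the order in which they are randomised could still matter even when someone else has judged eligibility.

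**Conclusion.** The point holds as a weakness in how concealment is secured. It is not a contradiction and not a shown bias. For a role that sees all allocations in one unstratified list and knows the block size, about 37 of 188 allocations are certain in advance and the best guess is right about two times in three. Several nurses who do not share what they know, or a stratified list, would change these figures. No effect on the hydroxyzine estimate can be calculated from the documents, and the sample size is unaffected. The improvement is cheap and worth making because it protects the only randomised contrast.

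**What to change.** 1. **Separate prediction from entry.** Have someone other than the unblinded nurse lock consent, eligibility and order of entry in REDCap before the randomise function opens. This matters most, because varying block sizes leaves best-guess accuracy close to where it is now. The cost is one form-lock rule and no extra staff.
2. **For any remaining patients, vary the block size.** Use undisclosed, randomly varying sizes that include sizes above 8. For example, 8/12/16 gives about 2% certain and about 64% best guess. A 4/6/8 mix also brings certain allocations to about 2% but leaves the best guess right about 68% of the time. The cost is a new allocation table and a slightly larger possible imbalance at the end of the list.
3. **Limit the concealment sentence.** Say that the unreleased list is hidden from the team and that the nurse learns each allocation when it is issued.
4. **If recruitment is complete, report a check.** Trial status gives 30 December 2019 as the planned end of recruitment, and the article is dated 2 January 2020, so items 1 and 2 may come too late. In that case report M0 m-YPAS by arm and by position in the block. No new data are needed. Places 7 and 8 hold only 2 × 23 = 46 children, so an unremarkable result would not exclude selection.

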## Discussion

POA is observed amongst children during their stay in the operative room with a prevalence of 83.3% [23]. Adverse psychological and behavioural changes (decrease in children’s self-esteem and emotional well-being, increased anxiety, sleep disturbances and social isolation) have been observed in a rate of 25% in children during hospital stay and even at 1-year post-discharge [6]. A recent systematic review also identified negative psychological sequelae in children [18].

The search for an ideal premedication drug to reduce POA in children is ongoing. The drugs used as anxiolytics are not exempt of side effects and the studies about this issue are limited to dental procedures [14–16]. One study [15] evaluated hydroxyzine at doses of 0.15 mg/kg, yet the dose proposed in our clinical trial is of 2 mg/kg.

The role of clowns and hydroxyzine in the management of anxiety is controversial as there are studies both for and against them [18–20]. We have not found any study that determines the additive effect on anxiolysis of distracting techniques with clowns and pharmacological treatment, as we propose in our case.

The proposed study has some limitations. The clowns are not always at the hospital; therefore, assignment to this intervention depends on whether they are present or not on the day of surgery. In order to reduce this bias, the healthcare professionals that plan the patient’s surgery will not know when the clowns come to the hospital.

The main objective of this study is the evaluation of POA. Studies that evaluate POA are difficult to perform and interpret, mostly because of the difficulty in assessing anxiety attributable to the surgical act. According to some studies [3, 25], the moment with the maximum rate of anxiety and fear associated with the entire surgical procedure is during anaesthetic induction. Therefore, evaluating the child’s anxiety during anaesthetic induction is very useful to determine whether the strategies used in the presurgical period have been effective in reducing anxiety [26]. That is the reason why in the present study, POA is evaluated in both moments. Most studies on this topic use a presurgical anxiety rating scale, the m-YPAS [23, 24, 26, 27].

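### Clown accompaniment is a non-random exposure set by the day of surgery, yet the plan labels it chance, puts it in the same group factor as randomised hydroxyzine, and assumes 47 per group

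*Protocol article*

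**What the plan says.** In the protocol article, Randomisation, the only randomised step is the drug: "randomisation to treatment with/without hydroxyzine will be performed". The ratio and blocks belong to that step: "Randomisation will occur in a 1:1 ratio in blocks of 8". The same section says that clown accompaniment "will depend on the clown presence/availability on the day of the intervention", with a code A or B recorded.

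The Abstract (Methods) describes the second split differently: after randomisation "they will be divided by chance into two further groups, depending on the presence of clowns" on the day of surgery. The Discussion lists the mechanism as a limitation, "assignment to this intervention depends on whether they are present or not on the day of surgery", and says that the staff who schedule operations will not know the clown days.

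Under Treatment guideline, eligibility is confirmed and the drug is randomised at this point: "On the day of surgery, once the IC and, if applicable, child agreements have been signed".

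Under Sample size, 47 per group is derived for hydroxyzine plus parents against parents alone and then applied to all four groups: "The final sample size would be 188 subjects (47 in each group").

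Under Data analysis, the main outcome goes into a repeated measures ANOVA with study group as the between-subject factor. Covariates enter only if baseline differences are judged relevant. No term for surgery day is described. The Discussion closes by saying that, if the hypothesis is confirmed, the combination may be considered the most effective and safe option, without noting that the clown part is not randomised.

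**The concern.** Availability on a given day is not a chance mechanism under the trial's control. Children operated on clown days may differ from the others in surgical list, team, type of operation or calendar period, and they share whatever else is particular to that day. The main objective in the Background is an additive effect of hydroxyzine and clowns. To say that the combination beats hydroxyzine alone, one needs group 4 v 3, and to say that clowns help on their own, one needs group 2 v 1. Both are non-randomised comparisons. If the plan is followed as written, they would be reported from the same factor and in the same terms as the randomised hydroxyzine contrasts, in a trial titled randomised and double-blind.

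Two smaller matters follow. Children who share a day may be correlated, so standard errors for clown contrasts may be somewhat too small. And since the clown share is not controlled, the four equal groups are not assured.

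**Working it through.** **Which contrasts are randomised**

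| Contrast | What differs | Basis |
|---|---|---|
| 3 v 1 | hydroxyzine, no-clown days | randomised |
| 4 v 2 | hydroxyzine, clown days | randomised |
| (4 v 2) minus (3 v 1) | interaction | compares two randomised drug effects; day effects common to both drug arms cancel |
| 2 v 1 | clowns, no hydroxyzine | day-level, not randomised |
| 4 v 3 | clowns, with hydroxyzine | day-level, not randomised |

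**The plan's own figure** (inputs from Sample size: difference 14.3; SDs 13.5 and 24.2; power 90%; level 0.025)

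Average-variance SD = √[(13.5² + 24.2²)/2] = √383.945 = 19.59.

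n = 2 × [19.59 × (2.241 + 1.282)/14.3]² = 46.6, rounded up to 47. Power at 47 is 90.3%. The figure reproduces with a two-sided 0.025 level; a one-sided 0.025 level gives 40. It is a calculation for the randomised contrast 3 v 1 with independent children. No effect size is given for clowns.

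**Clown share** (assumption: 94 children per drug arm, the same clown share p in both; the document gives no share)

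For 3 v 1, each group has 94 × (1 − p) children, SE = 19.59 × √(2/n), power = Φ(14.3/SE − 2.241).

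For a clown contrast within one drug arm, the groups have 94p and 94(1 − p), SE = 19.59 × √(1/n₁ + 1/n₂). This borrows the 14.3 points and assumes equal SD and no clustering.

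| Clown share | n in groups 1 and 3 | Power, 3 v 1 | Power, clown contrast |
|---|---|---|---|
| 30% | 65.8 | 97% | 84% |
| 40% | 56.4 | 95% | 89% |
| 50% | 47.0 | 90% | 90% |
| 60% | 37.6 | 82% | 89% |
| 70% | 28.2 | 69% | 84% |

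For 4 v 2 the 3 v 1 column reads in reverse order. If instead the clown group had SD 13.5 and the no-clown group 24.2, the clown contrast would have 92% at a 30% share and 76% at 70%.

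**Clustering by day** (cluster size and ICC are not in the document)

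Trial status gives recruitment from 12 January 2018 to 30 December 2019: 717 days, about 102 weeks. 188/102 is about 1.8 enrolled children per week. I therefore assume 1 to 2 enrolled children per operating day and ICC 0.02 to 0.10.

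Design effect = 1 + (m − 1) × ICC: 1.00 at m = 1, and up to 1 + 0.10 = 1.10 at m = 2.

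Actual size of a nominal 5% test = 2 × [1 − Φ(1.96/√DE)]: 5.0% at DE 1.00, and 2 × [1 − Φ(1.869)] = 6.2% at DE 1.10.

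**The case against.** Much can be said for the plan. The mechanism is not hidden: the Abstract sentence itself goes on to mention clown presence on the day, the Randomisation section treats clowns separately, Trial design limits the blinding to the drug, and the Discussion names the limitation. A reader might infer that the document claims clowns are randomised. It does not; the fault is the word chance and the absence of any distinction in the analysis and conclusion.

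A reader might also infer that the clown contrasts are in fact confounded. The document shows no imbalance, and keeping schedulers unaware of clown days guards against deliberate scheduling. What remains open is day-linked lists, teams and calendar time, and enrolment on the day itself, when clown presence may be visible. Baseline anxiety is measured at M0 and is among the repeated measures, and adjustment for relevant differences is foreseen. That helps, but adjustment that depends on what is observed is weak protection for a non-randomised contrast.

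On size, larger figures are tempting. With 3 to 6 enrolled children per day and ICC up to 0.10, the nominal 5% test would reach 11%. But 188 children at that rate means only about 31 to 63 enrolling days in two years, which the document does not exclude but nothing in it supports. The power of 82% or 69% is likewise not a general loss: it belongs to 3 v 1 at clown shares above one half, and the same contrast gains power below that.

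A model term for day is a detail that an analysis plan may carry. The labelling, the conditional adjustment and the closing conclusion are stated in this document and stand as written.

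**Conclusion.** The point holds. Only hydroxyzine is randomised; clown accompaniment is a non-random exposure at the level of the day, and the plan does not carry that distinction into its Abstract wording, its analysis or its conclusion. Contrasts 2 v 1 and 4 v 3 are open to confounding, of a size that the document gives no means to estimate. Contrasts 3 v 1 and 4 v 2, and the interaction as a comparison of those two drug effects, rest on randomisation.

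The 47 per group is correctly calculated but is an expectation under an equal clown share, not a property of the design; away from that share, power moves in either direction depending on the contrast. The error-rate effect of clustering is modest. The power and error-rate figures rest on the assumed clown shares, cluster sizes and ICCs set out above. The main harm is one of interpretation: an observational comparison would be read as randomised evidence for the combination.

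**What to change.** 1. Pre-specify that clown contrasts are always adjusted for M0 m-YPAS, age, type of surgery and calendar period, with a random effect for surgery day or standard errors clustered by day. M0, age and type of surgery are already collected, and the surgery date is known.
2. Replace the chance wording in the Abstract with assignment by clown presence on the day. State that hydroxyzine contrasts within clown and no-clown days are randomised, and that clown and combination-versus-hydroxyzine contrasts are not. Caveat the closing conclusion of the Discussion to match.
3. Restate 47 per group as the size expected under an equal clown share, and report the achieved group sizes and precision.

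The cost is a few model terms and some wording, slightly wider intervals for the clown contrasts, and a more modest claim. All of it can be done before analysis, whatever the state of recruitment.

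Stratifying the drug list by clown code and closing a stratum at 94 is not advised. Recruitment was due to end on 30 December 2019, before the article appeared on 2 January 2020, and closing a stratum would tie clown status to calendar time.
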